**Table 1 Tab1:**
[figure not shown]
SPIRIT figure

### Randomization

One hundred fifty patients with CP/CPPS were selected and will receive treatment in Zhongda Hospital affiliated to Southeast University from September 2022 to September 2023.

### Sequence generation

Randomization 1:1:1 is done using https://www.sealedenvelope.com/simple-randomiser/v1/lists with varying block randomization with a block size of 6. No stratification is used.

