### Study setting

This trial (NCT05659199—ClinicalTrials.gov) is a monocenter randomized controlled trial with three groups conducted in Department of Rehabilitation and the Department of Ultrasonography of Zhongda Hospital, Nanjing, Jiangsu, China. Zhongda Hospital is a teaching hospital, where the total number of outpatients annually is 2.03 million. The Zhongda Hospital has a dedicated Pelvic Floor Health Management Centre to assess, treat, and follow-up patients with pelvic floor dysfunction. Patients admitted to the Pelvic Floor Health Management Center include those seeking postpartum pelvic floor rehabilitation, those with chronic pelvic pain syndrome, and others with pelvic floor dysfunction. Treatment provided by the Pelvic Floor Health Management Center includes pelvic floor biofeedback electrostimulation, pelvic floor magnetic stimulation, extracorporeal shockwave therapy, and myofascial release therapy. Myofascial release therapy is a kind of manipulation therapy. Between 2020 and 2023, more than 1000 patients with pelvic floor dysfunction were treated at the Pelvic Floor Health Management Center. In this trial, the subjects included will be randomly assigned to the extracorporeal shockwave, myofascial release, and combined therapy groups.

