### Implementation

The randomization will be done according to the sealedenvelope.com algorithm. The participants will be enrolled after an outpatient visit, and on the following day, the participants will show up for the informed consent. The primary investigator will open the sealed envelope at the end of the baseline examinations.

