### Recruitment

When all criteria for participation are met, the patient can consider participation and ask questions to any therapist. If a patient decides to participate in the trial, the patient signs an informed consent form. Subsequently, the patient will be allocated to one of the three groups. Participants cannot switch from the extracorporeal shockwave, myofascial release, and combined therapy groups. However, a patient is allowed to withdraw from the trial without providing a reason for withdrawal and still receives usual care.

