### Sample size calculation

Previous studies showed that myofascial release therapy had notable effects [32] (corresponding to a Cohen’s *d* of about 0.5) on improving quality of life, prostate-related symptoms, and pain. The primary outcome will be the change in NIH-CPSI scores, the clinical response rate, and the remission rate as measured by the NIH-CPSI 4 weeks after the completed intervention. We assumed that extracorporeal shockwave combined with myofascial release therapy had similar effects on NIH-CPSI scores. A sample of 40 participants per group was computed by the G*power software to achieve a power of 60% and a level of significance of 5% and a 95% confidence level. To compensate for an estimated dropout rate of 25%, 150 participants will be ultimately required. (i.e., the number in each group is 50).

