This study innovatively uses the modulus of elasticity to assess pelvic floor muscle tone, which has previously been used to assess the muscle status of spastic muscles in hemiplegic patients with good sensitivity [48, 49]. In the course of the previous treatment, it was found that the pelvic floor muscles became less stiff and more elastic after myofascial release therapy, but the improvement in elasticity has not been assessed by objective criteria.

Sympathetic skin response is a transient potential change in the skin that is triggered by endogenous or exogenous stimuli. As a noninvasive test, SSR can be used clinically to detect disorders related to sympathetic tone [50]. Due to the extensive distribution of sympathetic postganglionic fibers in the skin and the fact that the nerves in the skin of the upper limbs and chest originate from the cervical and stellate ganglia, stellate ganglion nerve activity can be reflected by upper limb skin sympathetic nerve activity. Since reduction of CP/CPPS symptoms can significantly improve depression, anxiety, and pain symptoms of patients [16], we presume the possible pathogenesis of chronic pelvic pain syndrome may be the altered sympathetic nerve function caused by anxiety and depression.

This study will compare the agreement between patients’ sympathetic skin response and NIH-CPSI scores at different stages of treatment. If the results of this study show good linear correlations, it may suggest that one of the pathogenic mechanisms of CP/CPPS is hypo- or hyper-autonomic function and that more effective combination treatments could be developed by focusing on this pathogenesis in the future. This proposed study aims to contribute to this growing area of research by exploring the pathogenesis and novel therapeutic targets of CP/CPPS.

Moreover, the study may yield a limitation: we could only realize that participants and evaluators were blinded, and the therapist would know the grouping. We will try to improve our method in the follow-up research, trying to achieve the requirement that therapists be blinded.

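### The block scheme is called varying but only one size, 6, is given and published; if 6 is fixed, a fifth of allocations could be deduced by someone who knows all earlier ones in order

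*Protocol article*

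**What the plan says.** - **Scheme.** Under Sequence generation, allocation is equal across three arms ("Randomization 1:1:1 is done using" an online list generator), "with varying block randomization with a block size of 6", and "No stratification is used". Study setting adds that the trial "is a monocenter randomized controlled trial with three groups".
- **Size.** Sample size calculation states that "150 participants will be ultimately required", 50 per group.
- **Concealment.** Under Concealment mechanism, an outsider prepares numbered, opaque, sealed envelopes in advance. Investigators do not know the contents, and an envelope is opened only once consent is signed.
- **Opening.** Implementation says: "The primary investigator will open the sealed envelope at the end of the baseline examinations".
- **Contact before consent.** Recruitment says that once eligibility is met, "the patient can consider participation and ask questions to any therapist".
- **Who is unblinded.** The Discussion concedes that "the therapist would know the grouping".
- **Timing.** Trial status says that recruitment was still under way, so the block size became public during enrolment.

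**The concern.** The description of the scheme contradicts itself, and the only size given points to a fixed block of 6. With one centre and no strata there is a single sequence, so each patient's place in a block can be counted by anyone who has followed the list from the start. Envelopes protect the next assignment from being read. They give no protection against working it out from what has already been assigned.

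The stake is selection bias. If staff in contact with a candidate could foresee the next arm, they might encourage, delay or discourage that candidate before consent. Blinding participants and evaluators acts after allocation and would not undo this. NIH-CPSI, one of the two primary outcomes, is patient-reported, so an imbalance in baseline severity or expectation would bear on it directly. The other, sEMG, is measured by a device, but a difference in who is enrolled in each arm could affect it too.

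**Working it through.** **Inputs from the protocol article.** Three arms at 1:1:1, block size 6 (so two places per arm in each block), no stratification, one centre, 150 participants.

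**The plan's own figure.** 150 / 6 = 25 complete blocks, and 25 × 2 = 50 per arm, as stated. This fits a fixed block of 6 but does not prove it.

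**Assumption for the rest.** The observer knows that the block size is 6 and knows all earlier allocations in order.

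**Allocations known for certain**
- Position 6 is always determined.
- Position 5 is determined only if the last two places belong to the same arm. Of the 15 possible pairs of remaining places, 3 are same-arm pairs, so the probability is 3/15 = 0.2.
- Share: (1 + 0.2) / 6 = 20.0%. Expected number: 25 × 1.2 = 30 of 150.

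**Positions where at least one arm is ruled out**
- Positions 1 and 2: 0.
- Position 3: the first two are alike, 1/5 = 0.2.
- Position 4: the first three are not all different, 1 − (4/5 × 2/4) = 0.6.
- Positions 5 and 6: 1 each, because at most two places remain for three arms.
- Share: (0.2 + 0.6 + 1 + 1) / 6 = 46.7%. Expected number: 25 × 2.8 = 70 of 150.

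**Best guess (the arm with most places left)**

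| Position | Probability correct |
|---|---|
| 1 | 1/3 = 0.333 |
| 2 | 2/5 = 0.400 |
| 3 | 2/4 = 0.500 |
| 4 | 0.4 × 1/3 + 0.6 × 2/3 = 0.533 |
| 5 | 0.8 × 1/2 + 0.2 × 1 = 0.600 |
| 6 | 1.000 |

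Mean: 3.367 / 6 = 56.1%, about 84 of 150, against 33.3% by chance.

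**What mixing the sizes would change.** The protocol article names no other size, so the sets below are assumptions. The mixed rows come from a simulation of 400 lists of 150, with an observer who knows the set of sizes but not their order and updates by Bayes' rule. As a check, the simulation gave 20.0% and 56.2% for fixed 6, against the exact 20.0% and 56.1%.

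| Sizes | Known for certain | Mean correct guess |
|---|---|---|
| 6 (exact) | 20.0% | 56.1% |
| 3, 6 | 8.7% | 57.8% |
| 3, 6, 9 | 3.7% | 55.4% |
| 6, 9 | 5.1% | 54.2% |
| 6, 12 | 5.7% | 52.5% |
| 6, 9, 12 | 2.4% | 52.8% |

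With 3, 6 and 9, certain allocations fall by 20.0 − 3.7 = 16.3 per 100 patients enrolled under the new list. The average guess rate falls by only 56.1 − 55.4 = 0.7 percentage points.

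**The case against.** The concealment procedure is sound as far as it goes. Envelopes are opaque, numbered, prepared by an outsider and opened only after consent and baseline examinations, and questions to therapists come after eligibility is met. That narrows the room for steering. It does not meet the specific risk, because deduction uses only past assignments and a candidate can still be delayed or discouraged before consent.

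Four stronger readings are tempting, and the protocol article does not support them.

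- **That upcoming allocations are predictable.** The text also calls the blocks varying. If they are, the fixed-block figures do not apply. Even under a fixed 6, 80% of allocations are not determined.
- **That therapists know every earlier allocation.** The Discussion says that the therapist would know the grouping, as a limit on blinding. Nothing says that each therapist sees all allocations in order. A therapist who knows only some of them cannot reach the figures above.
- **That the primary investigator can act on the knowledge.** This role opens the envelopes and so learns the sequence, but the article does not say that it screens candidates, judges eligibility or takes consent. Harm needs that link, or the passing of information to someone who has it.
- **That the gap between 56% and 33% is the price of the fixed size.** Nearly all of it comes from blocking itself. Mixed sizes 3, 6 and 9 still give about 55%, and 3 and 6 give slightly more than fixed 6.

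What stands is the contradiction in wording and the share of allocations known for certain, which does depend on the fixed size.

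**Conclusion.** The point holds as a contradiction to be reconciled and, if the block is fixed at 6, as an avoidable weakness in allocation concealment. Its size is then 20% of allocations known for certain (about 30 of 150) and at least one arm excluded at 47% of positions (about 70 of 150).

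These are upper bounds. They rest on three assumptions: that 6 is the only size used, that someone knows the complete ordered list of earlier allocations, and that this person can influence who is enrolled next. The first follows the only size stated. The second is most plausible for the primary investigator, and perhaps partly true for therapists. The third is not stated. Nothing in the article shows that anyone tracks the list, so a reader should not infer that selection has occurred. The change is still worth making, because it removes most of the certain predictions at little cost.

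**What to change.** 1. Reconcile the wording under Sequence generation. If several sizes were in fact used, a text correction suffices, without giving the sizes to site staff.
2. If the size is fixed at 6, generate the list for patients not yet enrolled with randomly mixed sizes, for example 3, 6 and 9. Keep the sizes out of any document that enrolling and treating staff can read. Certain allocations fall from 20% to about 4%. The average guess rate hardly changes, so this step should not be presented as making allocation unguessable.
3. Optionally, if the outsider who prepares the envelopes can take on the task, let that person hold them and release each allocation after consent and baseline. This addresses what mixed sizes leave, because the running record of allocations would no longer build up with the envelope opener.

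**Cost.** Steps 1 and 2 need a new list and a new set of envelopes. The possible group imbalance is slightly larger: an unfinished block of 9 can leave two arms differing by up to 3, plus up to 2 if the present list is cut in mid-block, whereas 25 full blocks of 6 end exactly equal. Only patients still to be enrolled benefit, and the article does not say how many remain. Step 3 turns a one-off preparation into a continuing duty, so it cannot be assumed to need no extra staff time.

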### Concealment mechanism

The randomization sequence will be placed in sequentially numbered, sealed, and opaque envelopes. Sealed envelopes with extracorporeal shockwave therapy (1), myofascial release therapy (2), and combined therapy (3) will be made beforehand for the included trial participants by an outsider, and investigators will not know the content of the envelopes. After the patient signs the consent form, an envelope will be opened to assign an intervention for the patient.

### Implementation

The randomization will be done according to the sealedenvelope.com algorithm. The participants will be enrolled after an outpatient visit, and on the following day, the participants will show up for the informed consent. The primary investigator will open the sealed envelope at the end of the baseline examinations.

### Eligibility criteria

Patients with hormone abnormalities are excluded because thyroid dysfunction and testosterone may affect prostate function and myofascial status.

Participants will be screened using the following criteria.

Inclusion criteria:According to the National Institutes of Health classification of prostatitis [29], all male patients meet the diagnostic criteria for chronic prostatitis type IIIB/chronic pelvic pain syndrome (pain in the bladder, groin, perineal area, genitalia or lower abdomen with no significant abnormalities on urological examination);Patients are aged 20–40 years;Patients with chronic pelvic pain lasting over 6 months;Patients sign the informed consent form.

Exclusion criteria:Patients with significant coagulation disorders, perineal anatomical abnormalities, hormonal abnormalities, and neurological abnormalities;Patients with an apparent cause of pelvic pain, such as a history of previous surgery, chronic infection, trauma, prostatitis, and epididymitis;Patients receiving other treatments during the study;Patients with any urethral pathology;Patients who have had closed lumbar injections and previous lumbar surgery within 6 months;Patients with other conditions causing pelvic pain;Patients with contraindications to physiotherapy;BMI > 22.9

Termination and shedding criteria:Other serious illnesses occur in the course of treatment;Poor patient adherence and failure to complete the full course of treatment.

### Criteria for discontinuing or modifying allocated interventions

Patients receiving other treatments during the study will be excluded as exclusion criteria, but rehabilitation interventions will still be provided. Participants who experienced severe adverse events during the intervention will discontinue treatment, and the data that have been collected will be used for subsequent data analyses.

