### Strategies to improve adherence to interventions

Three groups of participants will be treated by specially trained therapists and the intervention process will strictly follow the study protocol. If the participant is not treated and evaluated at the specified time interval, the primary investigator will contact the participant to ensure that the intervention is proceeding rigorously. If the participant continues to be absent from the treatment as needed or firmly withdraws from the study, the relevant data that have been collected will be used for subsequent data analyses.

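### Patients who take other treatment after randomisation are excluded, with no statement that their data are kept; this can bias the comparison between arms

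*Protocol article*

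**What the plan says.** Four parts of the protocol article bear on this.

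- **Implementation** fixes the time of allocation: "The primary investigator will open the sealed envelope at the end of the baseline examinations".
- **Eligibility criteria** lists among the exclusions "Patients receiving other treatments during the study". Under a separate list of termination and shedding criteria it adds "Poor patient adherence and failure to complete the full course of treatment".
- **Criteria for discontinuing or modifying allocated interventions** applies the first of these to patients already in the trial: "Patients receiving other treatments during the study will be excluded as exclusion criteria". The same sentence adds that they go on receiving rehabilitation. Its next sentence deals with participants who have severe adverse events; they "will discontinue treatment, and the data that have been collected will be used for subsequent data analyses".
- **Strategies to improve adherence to interventions** covers participants who stay away from treatment or withdraw: "the relevant data that have been collected will be used for subsequent data analyses".

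The Statistical methods section neither repeats the exclusion nor overrides it.

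**The concern.** An eligibility criterion should be decidable before allocation. Whether a patient takes other treatment during the study is known only afterwards, so acting on it removes patients by something that happened under the assigned treatment.

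A patient whose pain is not improving has an obvious reason to look for other treatment. If such patients leave the analysis, the arm that loses more of them looks better than it was, and the groups compared are no longer those that were randomised. The article does not state this link with response. It is an inference, but a natural one in a pain trial.

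Follow-up is also at stake. The Sample size calculation section places the primary NIH-CPSI assessment 4 weeks after the completed intervention (T3). A patient excluded before then may have no primary outcome, and no later analysis rule can recover it.

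A second, smaller matter is that poor adherence and an incomplete course are called shedding criteria, while another section keeps the data of absent or withdrawing participants. The article does not connect the two, so shedding could be read as removal from the analysis.

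**Working it through.** **1. The passages side by side**

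| Event after allocation | What happens to the patient | What happens to the data |
|---|---|---|
| Other treatment taken | Excluded; rehabilitation still provided | Not stated |
| Severe adverse event | Treatment discontinued | Collected data used |
| Continued absence or withdrawal | Contacted by the investigator first | Collected data used |
| Poor adherence, incomplete course | Termination and shedding | Not stated under that criterion; absence is covered by the row above |

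Only the first row has no data rule anywhere in the article. Because rehabilitation goes on, exclusion there cannot simply mean stopping treatment. The natural reading is that the patient leaves the trial.

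**2. The plan's own figures (Sample size calculation section)**

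Inputs: d = 0.5, power 60%, significance level 5% (two-sided assumed), 25% dropout.

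- n per group = 2 × (1.960 + 0.253)² / 0.5² = 39.2, rounded up to 40. This reproduces the stated 40; a one-sided test would give 29.
- 40 × 1.25 = 50 per group, 150 in total, as stated.

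The yardstick for any bias is therefore 0.5 SD.

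**3. Size of the possible bias**

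The article gives no exclusion rates by arm, so these are assumptions:

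- The outcome is improvement, with SD 1.
- Exclusion follows a latent tendency with correlation ρ of 0.3 to 0.5 to poor outcome.
- The fraction p of an arm with the strongest tendency is removed.
- p is 15 to 25% in one arm and 5 to 10% in the other.

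The mean of those remaining rises by ρ × φ(z) / (1 − p), where z is the normal quantile that cuts off p. The factor φ(z) / (1 − p) is:

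| p | 5% | 10% | 15% | 25% |
|---|---|---|---|---|
| factor | 0.109 | 0.195 | 0.274 | 0.424 |

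The bias is ρ times the difference between the two arms' factors:

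| Removed | ρ = 0.3 | ρ = 0.5 |
|---|---|---|
| 15% v 10% | 0.024 SD | 0.040 SD |
| 15% v 5% | 0.050 SD | 0.083 SD |
| 25% v 10% | 0.069 SD | 0.114 SD |
| 25% v 5% | 0.095 SD | 0.158 SD |

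The range is 0.024 to 0.158 SD. Divided by 0.5, that is about 5 to 32% of the planned effect, in favour of the arm that loses more patients.

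**4. Other patterns, by simulation (50 per group)**

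- *No true difference, removal from one arm only.* Removing 5, 10, 15 or 25% of that arm, all from its lower half of responders, gives a false difference of 0.04, 0.09, 0.14 or 0.27 SD. The two-sided type I error becomes about 5.5, 7, 10 or 24%.
- *True d = 0.5, same response-dependent rule in both arms.* Removals of 10% v 6%, 15% v 9% and 25% v 15% shrink the observed difference to 0.49, 0.48 and 0.44 SD.
- *No true difference, same rule in both arms.* There is no bias.

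**5. Power (normal approximation, d held at 0.5)**

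- All 50 per group analysed: Φ(0.5 × √(50/2) − 1.96) = Φ(0.54) = 70.5%.
- 25% removed (37.5 per group): Φ(0.5 × √(37.5/2) − 1.96) = Φ(0.205) = 58.1%, just under the planned 60%.

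**The case against.** **The exclusion is not called an analysis rule.** It stands in a section on interventions, and exclusion is not defined there as removal from the analysis. That is correct. But the adjoining sentence shows that the authors state retention of data where they intend it, and continued rehabilitation rules out the reading that exclusion only means stopping treatment. Followed as written, the sentence takes a randomised patient out.

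**Adherence.** A reader might infer that the article gives opposite rules for the same non-adherent patient. The documents do not support that. The shedding criterion is silent on data, and the adherence section expressly keeps what was collected, so the two can be read together: participation ends and collected data are analysed. What stands is that the article should say so.

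**Other treatment.** A reader might likewise infer that the exclusion breaks a promise to use collected data. No such promise is made for these patients, so this is unequal handling and not a contradiction.

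**Bias and its direction.** It is tempting to say that the exclusion does bias the result and favours a particular arm. The article gives no exclusion rates by arm or reason. Discomfort from the rectal route, mentioned in the Background, does not separate the combined arm from the myofascial arm, because the combined arm receives the same myofascial therapy. With equal rules and no true difference there is no bias at all. So the claim must be that the exclusion can bias.

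**Matter for the SAP.** Analysis sets are commonly left to an analysis plan that is not shown, and their absence here is no finding. The point concerns an exclusion that the protocol itself states. An analysis plan could not restore assessments that were never made.

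**Conclusion.** The concern holds for patients who take other treatment. The protocol excludes them on an event seen only after randomisation and, unlike for severe adverse events, does not say that their data are kept. If exclusion is linked to poor response and its rate differs between arms, the comparison is biased towards the arm that loses more patients. Under the assumptions shown, the bias is about 0.02 to 0.16 SD (5 to 32% of the planned 0.5 SD). It can be nil if arms lose patients alike, and larger if one arm alone loses its poorer responders. These figures illustrate the possible size; they do not predict it.

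For poor adherence and incomplete courses the passages need to be reconciled, but they do not conflict outright.

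**What to change.** Amend the protocol as follows:

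1. State that taking other treatment, poor adherence or an incomplete course does not remove a randomised patient from follow-up or analysis.
2. In Eligibility criteria, confine the other-treatment exclusion to what can be established before the envelope is opened. Say that shedding does not mean removal from the analysis, in line with the adherence section.
3. Continue the already scheduled T1 to T3 assessments for these patients.
4. Record other treatment taken, with type and date.
5. Analyse all randomised patients in their allocated group, and use the present exclusions only for a per-protocol sensitivity analysis.

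None of this changes which treatment a patient receives or when it stops.

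The cost is a wording change and the effort of pursuing a few more visits already in the schedule. The effect estimate may be slightly diluted, because it will include patients who did not complete treatment or who took something else. The change should be made before patients are excluded, since missed assessments cannot be recovered.
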